#### Secondary research questions

The intervention is expected to influence different stigmatising attitudes and self-identification as mentally ill. Our secondary research questions are:
4.Does a conception of depression as a manifestation on a mental health-illness continuum favour the readiness for self-identification as mentally ill? Does it also have a reducing effect on stigmatising attitudes?H4: The agreement with continuum beliefs leads to higher self-identification (H4a) and reduces stigmatising attitudes (H4b).5.Does the strengthening of mental health literacy have a reducing effect on stigmatising attitudes and favour the readiness for self-identification as mentally ill?H5: The strengthening of mental health literacy leads to a higher self-identification (H5a) and reduces stigmatising attitudes (H5b).6.Can a biopsychosocial causal model of depression have a reducing effect on stigmatising attitudes? Does it also favour the readiness for self-identification as mentally ill?H6: The agreement with a biopsychosocial causal model leads to a higher self-identification (H6a) and reduces stigmatising attitudes (H6b).7.What importance does previous treatment experience have for the readiness for self-identification as mentally ill and the expression of stigmatising attitudes?H7: Positive treatment experience is associated positively with self-identification (H7a) and negatively with stigmatising attitudes (H7b).

#### Explorative research questions

In addition, open research questions pertain to how these intermediary variables interact with each other and, furthermore, influence help-seeking intention and behaviour as well as stigmatising attitudes, respectively. Also, the role of acute symptom severity on the whole process is unclear. Since no theoretically derived interaction could be hypothesised, the analyses will be explorative.

## Methods/design

A fractional factorial design is chosen, due to the number of influenced variables and the complexity of the study. This type of design will allow for an economic assessment, reducing the number of groups needed while ensuring that sufficient data for the primary and secondary outcomes can be collected. The conditions are systematically varied to determine the necessary within group condition-combinations after calculating the number of groups needed by multiplying the cartesian products of the variables with two and three levels, respectively: x = 3^2^ * 2^3^ = 72 (i.e., full factorial design). Fractioning the design by subtracting a variable-factor from the three-level variable resulted in our design (see Table 1) with a resolution of V and, therefore, being able to differentiate between main effects and two- (three-) way interactional effects: x = 3^2–1^ * 2^3^ = 24. For more information on fractional factorial designs refer to Dean et al. [15] and Siebertz, van Bebber, and Hochkirchen [55].

**Table 1 Tab1:** Fractional factorial design with 24 groups

Experimental group	Intervention content				
	Continuum belief	Mental health literacy	Causal belief	Self-efficacy (self-help)	Self-efficacy (treatment)
1 (control group)					
2				T	T
3		T			T
4		T		T	V
5			T		T
6			T	T	V
7		T	T		V
8		T	T	T	
9	T				T
10	T			T	V
11	T	T			V
12	T	T		T	
13	T		T		V
14	T		T	T	
15	T	T	T		
16	T	T	T	T	T
17	V				V
18	V			T	
19	V	T			
20	V	T		T	T
21	V		T		
22	V		T	T	T
23	V	T	T		T
24	V	T	T	T	V

*Note.* T = text-based intervention, V = video-based intervention. Information for both intervention-types are the same. The groups are determined through a priori systematic variation and fractioning of the condition-combinations. The design has a resolution of V and can statistically differentiate between main and two- (three-) way interactional effects

The first part of the study will be separated into two different assessment times, both taking about 25 min to be administered, allowing for a collection of pre- and post- intervention data. During the baseline assessment participants will answer questionnaires and will be asked to participate in the second part of the study, to which they will receive an e-mail invitation 36 h later. In the second part of the study all participants will receive the online intervention (see Intervention), after which the post-assessment is administered. The participants will be informed that they will be receiving an invitation via e-mail to participate in the three- and six-month follow-up assessment.

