### Study information

#### Power & sample size

The required sample size is based on calculations for ANOVA (repeated measures, within-between interaction) expecting small effect sizes of *f* = 0.10 due to the limited intervention administration time and the online setting. A significance level of α = 0.05 and a power of *1-*β = 0.95, as well as the a priori determined 24 groups were included in the calculation. The free software G*Power [16] was used to calculate the required sample size of *N* = 840. This would mean *n* = 35 in each group. To stray on the side of safety we strive to recruit *n* = 40 for each group, a total of *N* = 960 participants, to complete the second follow-up after 6 months of intervention administration. Based on previous experience we estimate a drop-out rate of 47% between the first assessment time and the second follow-up 6 months later, we aim to recruit *N* = 1.800 at the beginning of the study (see Fig. 2).

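### The 24-group fraction is not resolution V: it can estimate the main effects, but not main effects with all two-way, let alone three-way, interactions

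*Protocol article*

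**What the plan says.** The Methods/design section starts from the full crossing, "x = 3^2^ * 2^3^ = 72 (i.e., full factorial design", and removes one three-level factor from the exponent to reach 24 groups. Table 1 lists them. Continuum belief and self-efficacy (treatment) each have three levels (none, text T, video V). Mental health literacy, causal belief and self-efficacy (self-help) each have two (none, T).

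The section describes the fraction as "with a resolution of V and, therefore, being able to differentiate between main effects and two- (three-) way interactional effects", and the Table 1 note repeats it: "The design has a resolution of V and can statistically differentiate between main and two- (three-) way interactional effects". The note also says of text and video: "Information for both intervention-types are the same".

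Under Explorative research questions, "open research questions pertain to how these intermediary variables interact with each other", with the qualification: "Since no theoretically derived interaction could be hypothesised, the analyses will be explorative". The sample size section uses "ANOVA (repeated measures, within-between interaction) expecting small effect sizes of *f* = 0.10" and takes the 24 groups as an input.

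**The concern.** Resolution V means that no main effect or two-way interaction is aliased with any other main effect or two-way interaction, so all of them can be estimated in one model. A design with 24 distinct cells yields 24 cell means and cannot support a model with more than 24 parameters, whatever the number of participants per cell. Counting the parameters implied by the article's own factor levels shows that the limit is exceeded before any three-way term is added.

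The article gives this property as a feature of the chosen fraction and then poses questions about how the intermediary variables interact. An analyst who relies on the statement and fits all two-way terms would find two of the five randomised main effects, and almost all the interactions, not separately estimable. Any interaction result would then depend on which terms were left out, and the article does not say which are assumed to be zero.

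**Working it through.** **Inputs.** Factor levels and the 24 rows come from Table 1. Label continuum belief A, literacy B, causal belief C, self-help self-efficacy D and treatment self-efficacy E, and code none/T/V as 0/1/2.

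**The article's own counts.** 3² × 2³ = 72 and 3¹ × 2³ = 24 are both right. All 24 rows satisfy E = (A + B + C + D) mod 3, so Table 1 is a properly built one-third fraction. Only the resolution statement fails.

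**Parameter count, three-level coding.**

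| Terms | Parameters |
|---|---|
| Intercept | 1 |
| Main effects: 2 + 1 + 1 + 1 + 2 | 7 |
| A×E: 2 × 2 | 4 |
| AB, AC, AD, BE, CE, DE: 6 × 2 | 12 |
| BC, BD, CD: 3 × 1 | 3 |
| **Total with all two-way terms** | **27** |
| **Total with three-way terms added (25 more)** | **52** |

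**Rank of the Table 1 model matrix.**

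| Model | Columns | Rank |
|---|---|---|
| Main effects | 8 | 8 |
| Plus all two-way | 27 | 24 |
| Plus all three-way | 52 | 24 |
| All two-way except A×E | 23 | 23 |
| T and V collapsed, all two-way | 16 | 16 |
| T and V collapsed, all three-way | 26 | 22 |

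**What is separately estimable in the 27-column model.** A: 0 of 2 df. E: 0 of 2. A×E: 1 of 4. The other nine interactions: 0 df each. B, C and D: 1 of 1 each.

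**Orthogonality.** The A by E cross-table of groups is 2/3/3, 3/2/3, 3/3/2. It cannot be balanced, because 24 is not a multiple of 9. The largest contrast correlation is 0.217 between a main effect and a two-way interaction (for example A with BE) and 0.375 between two two-way interactions (for example AB with CE). The generalised word-length pattern is A₂ = 0.031, A₃ = 0.281, A₄ = 0.844; resolution V requires all three to be zero. For these factor levels, an orthogonal design of resolution V needs a number of cells divisible by 36 (3·3·2·2) and by 24 (3·2·2·2), hence by 72, which is the full factorial.

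**Variance relative to the full factorial at equal N.**
- Main-effects model: 1.016 for A and E; 1.00 for B, C and D.
- 23-parameter model: 1.48 for the A and E main effects, 1.78 for interactions involving A or E, and 1.00 for B, C, D and the interactions among them.

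**Sample size.** N = 840 is reproduced by the G*Power within-between formula with two measurements and a correlation of 0.5. The article does not state these two values, so they are assumptions. The formula gives 825, rounded up to 840 as a multiple of 24. It does not depend on the resolution, so this figure is untouched.

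**The case against.** The best defence is that no planned analysis is shown to fail. The Statistical methods section lists families of methods and never specifies a model with all two-way terms. The interactions are declared exploratory. Each of the ten two-way interactions is estimable when added alone to the main effects, and nine of the ten fit together. All of this stands, and it limits the consequence; it does not make the resolution statement true.

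A second defence is that text and video carry the same content and could be pooled. The two-way model then fits. But the article does not plan pooling, its 3² notation treats the formats as separate levels, and even after pooling the three-way model fails (26 parameters, 22 distinct cells).

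A third is that details belong in an analysis plan that is not shown. Here, though, the article makes a positive statement that is incorrect, and no analysis plan can make 24 cells estimate 27 parameters.

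A reader might also infer that the randomised tests of H2b and H2c, and so the test on help-seeking behaviour, are broken. The documents do not support that. It would require those hypotheses to be tested by the self-efficacy (treatment) main effect inside the full two-way model, which is nowhere planned; the article says that the self-efficacy scales will be used to test H2. In a main-effects model the factor is estimated almost without loss.

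**Conclusion.** The resolution V claim, made twice, is wrong, and so is the claim to separate three-way effects. Under the article's coding, 27 parameters are needed for main and two-way effects and 52 with three-way effects, against rank 24. These counts are exact and rest only on Table 1 and the levels it defines.

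The size of the problem is bounded. Main effects are estimable with 1.6% variance inflation, on the usual assumption that omitted interactions are negligible, and the literacy, causal-belief and self-help main effects remain estimable even in the 27-column model. What is affected is the stated justification of the design, the exploratory interaction analyses, and the two three-level main effects in any model that includes interactions. The trial is not invalidated and the sample size is unaffected. This should be fixed, but it does not threaten the trial.

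**What to change.** 1. Delete the resolution V and three-way statements from the Methods/design text and the Table 1 note. Say instead that the fraction supports all main effects and a limited set of two-way interactions, and give the generator or alias structure.
2. Estimate the randomised factor effects in one joint model containing all five factors, because the two three-level factors are slightly non-orthogonal. State that the three-level main effects assume omitted interactions are negligible.
3. Name one estimable interaction model in advance for the exploratory questions. The choices are:
   - all two-way terms except continuum belief × self-efficacy (treatment): 23 parameters, full rank, at 1.48 times the variance for three-level main effects and 1.78 times for interactions involving them, with the omitted interaction assumed to be zero; or
   - text and video collapsed to any versus none: 16 parameters, full rank, giving up the comparison of formats.

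The cost is a change of wording and one fixed model. No extra participants are needed. What is lost is a set of interaction claims that the design cannot support.

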### Study information

#### Power & sample size

The required sample size is based on calculations for ANOVA (repeated measures, within-between interaction) expecting small effect sizes of *f* = 0.10 due to the limited intervention administration time and the online setting. A significance level of α = 0.05 and a power of *1-*β = 0.95, as well as the a priori determined 24 groups were included in the calculation. The free software G*Power [16] was used to calculate the required sample size of *N* = 840. This would mean *n* = 35 in each group. To stray on the side of safety we strive to recruit *n* = 40 for each group, a total of *N* = 960 participants, to complete the second follow-up after 6 months of intervention administration. Based on previous experience we estimate a drop-out rate of 47% between the first assessment time and the second follow-up 6 months later, we aim to recruit *N* = 1.800 at the beginning of the study (see Fig. 2).

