## Background

Epidemiological studies show that even in countries with well-developed primary care and specialised mental health services most people with a mental illness do not seek treatment for their disorders, or only after considerable delay [6, 63]. In Germany two thirds of people with depressive symptoms do not seek mental health care [44]. This gap between health care need and utilisation exists despite modern developments in health promotion as well as selective preventive efforts such as mental health awareness campaigns. Moreover, people are systematically labelled and stigmatised for their mental illness [11, 38, 45]. People with a mental illness are often seen as dangerous, unpredictable, unreliable, and not normal [3]. The societal stigmatisation of people with a mental illness can be seen on many different levels, whether it is in personal day to day interactions, in working environments, on an institutional level, or in the media [11, 29]. A person with a mental illness who is aware of, agrees with, and internalises publicly endorsed stigmatising stereotypes, self-stigmatises and can experience loss of self-esteem, shame, and helplessness, inhibiting help-seeking behaviour [11, 47]. Therefore, it is important to address stigma in interventions supporting health care utilisation.

In a previous project the direct impact of stigmatising attitudes on help-seeking behaviour was examined. Results showed that stigmatising attitudes were negatively associated with a perceived need for help [59] and the use of professional psychiatric and psychotherapeutic help (β = − 0.19, *p* = 0.08). Furthermore, the main predictor for health care utilisation was the intention to seek help, which explained 22–37% of the variance of actual help-seeking behaviour and was especially strong for seeking psychotherapeutic help (β = 0.31, *p* < 0.001 [60];). Additionally, further findings concerning the self-identification as mentally ill [57], as well as a subjective sense of illness [58] and their respective association with help-seeking intention and behaviour were considered. On the basis of these findings it became evident that the working model had to be extended by one superordinate and five intermediary variables to account for the complex ways in which stigma impacts the help-seeking process. We use this extended and newly explicated model as the theoretical foundation of our present study.

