### Research agenda of the current study (stigma-II)

The present study will examine the effects of a short, informational, one-time administered intervention, aimed at influencing the intermediary process variables (i.e., continuum belief of mental illness, mental health literacy, causal beliefs, and self-efficacy to help oneself as well as seeking professional help) which in turn will reduce stigmatising attitudes and facilitate help-seeking.

The study will focus on people with at least mild depressive complaints, who are currently not receiving professional psychiatric/psychotherapeutic treatment, and live in Germany. Possible effects of the Covid-19 pandemic are assessed (e.g., adherence to regulations, mental-health burden through regulations), since it is assumed that the pandemic and lockdown-regulations had an impact on psychological well-being in general [14].

Participants of the experimental groups will receive a text-based vignette followed by a combination of online-administered interventional vignettes (either as a text and/or a video) designed to influence the five intermediary process variables described above. The participants of the control group will only be presented with the case-vignette. The primary and secondary outcomes will be measured directly pre- and post-intervention, as well as after 3 and 6 months in subsequent follow-up assessments. The primary outcome “help-seeking behaviour” will be assessed at the subsequent follow-ups. The study is designed as a quasi-experimental online study and the chosen design of experiment is the fractional factorial design [15] to adequately account for the complexity of all the possible intervention-combinations required to answer the research questions.

Prospectively, the study’s results will lead to a better understanding of the complex interplay between stigmatising attitudes and mental health care utilisation and which intermediary mechanisms play a pivotal role therewith. Moreover, the results could be used to design population wide prevention campaigns to encourage help-seeking when suffering from depressive complaints, on the one hand, and reduce stigmatising attitudes, on the other hand.

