### Outcome measures

Table 2 shows the variables that will be investigated at different times during the study and the instruments used to assess these. They have been classified into general psychological, intermediary process, help-seeking, stigmatisation, and context assessment measures. The final selection of the instruments, some adapted to fit the current research setting, were based on theoretical research and pre-study test results (*N* = 227), in which psychometric properties, especially of the adapted instruments, were analysed.

**Table 2 Tab2:** Questionnaires employed at the different study assessment times

Study assessments & measures	Number of items	Study time points			
		T0	T1	T2	T3
Socio-demographic					
Gender	1	X			
Month& year of birth	2	X			
Family status & partner	3	X			
Education	2	X			
Employment	2	X			
Income	1	X			
General psychological					
Subjective general health (SF-1)	1	X		X	X
Quality of life (EUROHIS-QoL Index)	8		X	X	X
Self-construal Scale (SCS)	24	X			
Subjective Socio-Economic Status	1				X
Intermediary process					
Continuum beliefs (CB_new)	12	X	X	X	X
Causal beliefs (List)	18	X	X	X	X
Mental health literacy, depression specific (D-Lit)	12	X	X	X	X
Self-efficacy to help oneself	6	X	X	X	X
Self-efficacy to seek out professional help	7	X	X	X	X
Help-seeking					
Subjective sense of illness (B-IPQ-R)	9	X		X	X
Self-identification as mentally ill (SELF-I)	5	X	X	X	X
Attitudes towards help-seeking (ATSPPH-SF)	10	X	X	X	X
Motivation behind help-seeking (ACMQ)	6	X	X		
Help-seeking intention (List)	16	X	X	X	X
Help-seeking subjective norms, attitudes and perceived control (TPB)	10	X	X	X	X
Help-seeking behaviour/ health-care utilisation	18			X	X
Stigmatisation					
Perceived public stigma and the agreement with stigma (SSMIS-public & -self-SF)	10	X	X	X	X
Social distance stigma (SDS)	7	X	X	X	X
Discrimination of mental illness	3	X	X	X	X
Sense of blame for mental illness	4	X	X	X	X
Self-stigma for seeking out professional help (SSOSH-SF)	3	X	X	X	X
Shame for being mentally ill and seeking out help	2	X	X	X	X
Emotional reaction towards a person with mental illness (ERMIS)	10	X	X	X	X
Context					
Depressive Symptoms (PHQ-9)	9	X	X	X	X
Anxiety Symptoms (PHQ-anxiety module)	7		X		
Differential diagnosis	1		X		
Previous treatment experience	3–7		X		
Perceived availability and accessibility to the health care system	1–5		X		
Covid-19 questions	4	X		X	X
	∑ = 246				

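### The only stated power (95%) is for a 24-group by time interaction; it does not carry over to H2c on the primary outcome, help-seeking behaviour, which is measured only after the intervention and has no power statement of its own

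*Protocol article*

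**What the plan says.** **Sizing.** The section on power and sample size in the protocol article rests on one calculation: "The required sample size is based on calculations for ANOVA (repeated measures, within-between interaction) expecting small effect sizes". It uses f = 0.10, alpha 0.05 and power 0.95, and says of the number of groups: "as well as the a priori determined 24 groups were included in the calculation". The result is N = 840 (35 per group), rounded up to 40 per group, N = 960, completing the 6-month follow-up. The number of measurements and the correlation between them are not stated.

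**Primary outcome.** The research agenda section says: "The primary outcome “help-seeking behaviour” will be assessed at the subsequent follow-ups". The abstract also places it at 3 and 6 months. In Table 2 the row "Help-seeking behaviour/ health-care utilisation" carries two marks, which the abstract and research agenda identify as T2 and T3. The sentence in the research agenda just before the quoted one, however, has primary and secondary outcomes measured directly before and after the intervention as well as at both follow-ups.

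**Hypotheses.** Among the primary research questions, H2c predicts that strengthening self-efficacy to seek professional help raises help-seeking behaviour. The introduction to those questions speaks of higher rates of utilisation. H1, H2a and H2b concern intention, which Table 2 schedules at T0 to T3. H3c concerns behaviour too, but as an association with earlier treatment experience, which is not randomised.

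**The concern.** A within-between interaction asks whether the groups change differently over time. For an outcome measured before and after the intervention, that is the intervention effect. For behaviour, measured only afterwards, the question in H2c is whether the level differs between the levels of one factor. That is a between-group comparison, with a different noncentrality and, for one factor, different degrees of freedom. The sizing therefore describes a test that does not answer H2c.

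At stake is how the primary result is read. If H2c comes out null, a reader will judge it against a type II error of 5% that was never calculated for it.

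**Working it through.** **1. Reproduce the plan's figure.** For the within-between interaction, lambda = f²·N·m/(1 − rho), df1 = (24 − 1)(m − 1), df2 = (N − 24)(m − 1). Assume m = 2 measurements, rho = 0.5 and no sphericity correction.
- N = 840: lambda = 0.01 × 840 × 2/0.5 = 33.6 on 23 and 816 df, power 0.954.
- N = 816, the next smaller balanced size: power 0.947.

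So 840 is the smallest balanced N reaching 0.95, and the stated figure is reproduced. At N = 960 the same test has power 0.979. Other inputs also return 840: m = 3 with rho = 0.42, or m = 4 with rho = 0.34. With rho = 0.5, m = 3 would give 720 and m = 4 would give 648. The stated N fits a two-measurement calculation but does not prove it.

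**2. What changes for behaviour.** Compared at one follow-up, lambda = f²·N = 0.01 × 960 = 9.6. The interaction formula gives 38.4 at the same N and f, four times as much. Averaging T2 and T3 gives lambda = f²·N·2/(1 + rho), which is 11.3 at rho = 0.7 and 14.8 at rho = 0.3.

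**3. Power for behaviour at f = 0.10, alpha 0.05 (noncentral F).** In Table 1 the self-efficacy (treatment) factor has three levels (none, text, video) with 8 groups each, so its overall test has 2 df.

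| Test | One follow-up, N = 840 | One follow-up, N = 960 | Mean of T2 and T3, N = 960, rho 0.7 to 0.3 |
|---|---|---|---|
| 24 groups, 23 df | 30% | 35% | 42-56% |
| Three-level factor, 2 df | 74% | 80% | 86-94% |
| One contrast, 1 df | 83% | 87% | 92-97% |

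**4. As a rate.** The article gives no expected rate. At N = 960, 8 × 40 = 320 people have no treatment self-efficacy content and 640 have some. Two-proportion normal approximation, two-sided alpha 0.05, over assumed rates without the content:

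| Assumed rate without the content | Power, 5-point gain | Power, 10-point gain |
|---|---|---|
| 10% | 58% | 98% |
| 15% | 47% | 96% |
| 20% | 41% | 92% |
| 30% | 34% | 86% |

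**5. Baseline covariate.** Help-seeking intention is collected at T0. Of intention in the previous project, the background section says: "which explained 22–37% of the variance of actual help-seeking behaviour". Under a linear approximation lambda becomes 9.6/(1 − R²). For the 2-df test at one follow-up:
- R² = 0.10: lambda 10.7, power 84%
- R² = 0.22: lambda 12.3, power 89%
- R² = 0.37: lambda 15.2, power 95%

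**The case against.** Four arguments on the other side have weight.

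- **An interaction can be computed.** A reader might infer that behaviour cannot have a group by time interaction at all. That goes too far: T2 and T3 are two time points, and the two-measurement formula would give that interaction about 98% power at N = 960 with rho = 0.5. But it tests whether groups diverge between 3 and 6 months. A benefit present at 3 months and held at 6 months would produce no interaction, so it does not answer H2c.
- **There is no single true power.** A reader might also infer that the real power is generally far below 95%. The article does not support that. It gives no rate, correlation or test for behaviour. Far below is right for a 24-group comparison, but H2c concerns one factor. One-factor tests on the mean of the follow-ups reach 86-97%, and a 10-point gain from 10% reaches 98%.
- **The calculation is apt for part of the trial.** Intention (H1, H2a, H2b) has pre- and post-intervention values. An N that is generous for single-factor tests on such outcomes is not an error.
- **The test for H2c may be fixed elsewhere.** The statistical methods section lists several methods, chi-square tests among them, and assigns none to H2c. It would be wrong to say that the plan analyses H2c by chi-square, and leaving the assignment to an analysis plan is no fault.

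What remains is that the article itself states the power basis and the outcome schedule, and the two do not fit for its named primary outcome. A fuller document could add a power statement for H2c but would not make this one apply.

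**Conclusion.** The point holds in limited form. The stated power of 0.95 belongs to a 24-group by time interaction. It can describe outcomes with a pre-intervention value; it does not describe H2c on help-seeking behaviour, for which no power is given.

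With f = 0.10 at N = 960, a one-factor test at a single follow-up has a type II error of about 13-20%, against the 5% a reader would take from the sample-size section. Averaging the two follow-ups narrows the gap to about 3-14%. Small gains in a rate are poorly covered (34-58% for 5 points); larger ones are well covered (86-98% for 10 points).

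These figures rest on assumptions: that f = 0.10, set for an interaction, carries over to a difference in level; a T2-T3 correlation of 0.3 to 0.7; rates of 10-30% without the content; and 40 completers in every group. The planned N is not shown to be inadequate. It is the power statement that needs correcting.

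**What to change.** 1. Keep N.
2. In the sample-size section, limit the 95% statement to outcomes with a pre-intervention value, and state the number of measurements and the correlation used.
3. Add a separate statement for H2c: the factor contrast, whether one follow-up or both are used, and the power or detectable difference over a range of assumed rates, as in the tables above.
4. In the research agenda section, reconcile the sentence that has primary outcomes measured before and after the intervention with the T2 and T3 schedule for behaviour.
5. Optionally, adjust the H2c analysis for T0 help-seeking intention. The gain is uncertain: it assumes that the explained variance from the previous project carries over, and the linear formula is only approximate if behaviour is analysed as a rate.

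The cost is rewording plus, for the optional step, one covariate already collected. No further participants or assessments are needed. The price is a less favourable stated power for the primary outcome.

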### Statistical methods

To answer the various research questions, the following statistical methods will be used: correlation analyses, (OLS-) regression analyses, multivariate analysis of variance with repeated measurements, multilevel analysis and Chi-square tests. Path models will be used to analyse the extended help seeking process-model. Appropriate statistical software (IBM SPSS 27, IBM AMOS, Stata, Mplus) will be used for all statistical analyses.

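### The sizing test is a pre-post change-score comparison, and the article does not commit to T0 adjustment, which would estimate the same effects with less variance at no cost

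*Protocol article*

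**What the plan says.** Power & sample size bases the trial on "calculations for ANOVA (repeated measures, within-between interaction) expecting small effect sizes of" f = 0.10. It adds "A significance level of α = 0.05 and a power of *1-*β = 0.95" and says that "the a priori determined 24 groups were included in the calculation". G*Power was then used to "calculate the required sample size of *N* = 840", or 35 per group. Neither the number of assessments nor their correlation is given.

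Statistical methods names "multivariate analysis of variance with repeated measurements" alongside correlation, OLS regression, multilevel analysis, chi-square tests and path models. It ties none of them to a hypothesis, and it neither names nor excludes T0 as a covariate.

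Methods/design splits the first part of the study into two assessments, "allowing for a collection of pre- and post- intervention data", with the invitation to the second sent 36 h after the first. Table 2 places help-seeking intention, self-identification (SELF-I) and the stigma scales at T0 and T1 (and at T2 and T3). Help-seeking behaviour appears at T2 and T3 only. The abstract states that allocation is random and takes place after the baseline assessment.

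**The concern.** The only test that the article specifies in any detail is the repeated-measures interaction. With two assessments, that test is an analysis of variance of T1 minus T0. Because participants are randomised after T0, all 24 groups share the same expected T0 mean. The change score ignores this. It subtracts the whole T0 value, noise included, where only part of it predicts T1. A regression of T1 on T0 and allocation gives T0 its proper weight, targets the same allocation effect and never has the larger variance.

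At stake is precision for intention (H1, H2a, H2b) and for self-identification and stigma (H4 to H6). The article itself expects small effects for a short, single intervention, so precision that comes free with data already collected is worth having.

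**Working it through.** **Inputs from the article.** f = 0.10, α = 0.05, power 0.95, k = 24 groups, N = 840 (Power & sample size).

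**Inputs assumed.** m = 2 assessments, correlation ρ = 0.5 and sphericity. They are inferred because they reproduce 840.

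**1. Reproduce N = 840.** For the within-between interaction, λ = f²·N·m/(1 − ρ), with df₁ = (k − 1)(m − 1) and df₂ = (N − k)(m − 1).

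- λ = 0.01 × 840 × 2/0.5 = 33.6, with df 23 and 816. Power is 0.9545.
- The smallest N that reaches 0.95 is 825. In equal groups this becomes 24 × 35 = 840, the article's figure.
- At the same ρ = 0.5, three assessments give 720 and four give 648. Three or four assessments could reach 840 only at some correlation between 0.3 and 0.5 (1,008 down to 720 for three, 888 down to 648 for four). The two-assessment reading is therefore the natural one, but it remains an inference.

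**2. Compare the variances.** Take variance σ² at each assessment.

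- Change score: 2σ²(1 − ρ)
- T1 adjusted for T0: σ²(1 − ρ²)
- Ratio, adjusted to change score: (1 + ρ)/2
- Fraction removed: 1 − (1 + ρ)/2 = (1 − ρ)/2

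| ρ | 2(1 − ρ) | 1 − ρ² | Variance removed |
|---|---|---|---|
| 0.3 | 1.40 | 0.91 | 35% |
| 0.42 | 1.16 | 0.82 | 29% |
| 0.5 | 1.00 | 0.75 | 25% |
| 0.7 | 0.60 | 0.51 | 15% |
| 0.75 | 0.50 | 0.44 | 12.5% |
| 0.84 | 0.32 | 0.29 | 8% |
| 0.9 | 0.20 | 0.19 | 5% |

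The values 0.42, 0.75 and 0.84 are retest correlations quoted in Outcome measures: B-IPQ-R items over 6 weeks, and the PHQ-9 over 48 h. They belong to other scales and serve only to mark a plausible range.

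**3. Carry this into the sized test.** Adjustment multiplies λ by 2/(1 + ρ) and costs one degree of freedom.

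- At ρ = 0.5 and N = 840: λ = 33.6 × 1.333 = 44.8, and power rises from 0.954 to 0.993.
- N for 95% power in equal groups falls from 840 to 624 at ρ = 0.5, from 504 to 432 at ρ = 0.7, and from 360 to 312 at ρ = 0.8.

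**4. Illustrate with a single two-level module.** Mental health literacy, causal belief and self-help self-efficacy are each given in 12 of the 24 groups (Table 1). Take 480 versus 480 and d = 0.15. The d is an assumption. The 960 is the article's target for 6-month completers, and numbers at T1 should be at least that large. With v the variance from step 2, SE = √(2v/480) and power = Φ(d/SE − 1.96).

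- ρ = 0.5: SE 0.0645 versus 0.0559, power 0.64 (change score) versus 0.77 (adjusted)
- ρ = 0.7: 0.85 versus 0.90
- ρ = 0.84: 0.984 versus 0.990

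Continuum belief and treatment self-efficacy have three levels of eight groups each, so this contrast does not describe them. The variance ratio applies to them unchanged.

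**The case against.** The strongest reply is that the article never says these outcomes will be analysed by change scores. The sentence on the interaction explains N. The methods list also contains OLS regression and multilevel models, either of which can carry T0, and the choice may sit in an analysis plan that is not shown. This stands. A reader might infer that the repeated-measures interaction is the fixed analysis of every pre-post outcome, and the text does not support that. What remains is that the one test described in detail, and matched by an entry in the methods list, is the less efficient one, with no commitment to the better one.

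Second, sizing on a less efficient test is cautious and not wrong. This also stands: under its own inputs, 840 gives the stated 95% power.

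Third, the 25% depends on an unstated ρ. With the T1 invitation sent 36 h after T0, ρ may be well above 0.5 and the gain nearer 8 to 15%. Where ρ is high, change-score power is already high and moves little, as step 4 shows. This stands, and it limits the size of the point. Nor is a quarter an upper limit, since the gain exceeds 25% below ρ = 0.5.

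Fourth, a reader might take chance T0 differences between small groups (standard error 1/√40 = 0.16 SD to 1/√35 = 0.17 SD) as regression to the mean that biases the results. Under randomisation such differences are imprecision, already covered by the test's type I error. For a module averaged over 480 participants the figure is only 1/√480 = 0.046 SD.

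Fifth, if all four assessments enter one model, the interaction is no longer a simple change score. That is correct, and the algebra here is for T0 and T1 only.

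None of these replies reverses the direction: (1 + ρ)/2 is below 1 for every ρ below 1.

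**Conclusion.** The point holds as one of efficiency. For outcomes measured at T0 and T1, committing to T0 adjustment removes a fraction (1 − ρ)/2 of the change-score variance: 25% at the inferred ρ = 0.5, 15% at 0.7, 8% at 0.84. The result rests on random allocation after T0, equal variances at the two assessments, a linear relation between T0 and T1, and a two-assessment comparison.

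It does not show a biased analysis, an incorrect sample size or an overstated power. It does not reach help-seeking behaviour (H2c), which has no T0 value, or H3 and H7, which concern treatment experience that is observed and not allocated. The change is worth making because it is free, but its benefit is modest if ρ is high.

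**What to change.** For outcomes measured at T0 and T1 (H1, H2a, H2b, H4 to H6), name as the main analysis a linear model of the T1 value on the five allocated modules plus the T0 value of the same scale. Enter continuum belief and treatment self-efficacy with three levels and the other modules with two. An equivalent choice is a multilevel model with one common T0 mean, that is, no group effect at T0. A multilevel model that lets group means differ at T0 would not give the gain. Keep the time-by-group interaction as a sensitivity analysis.

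The cost is wording only. Both model types are already among the listed methods, all T0 values are already collected, and neither the sample size nor the schedule changes.
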